### Masking Procedures

This study will be open label.

### Reasons for Withdrawal

Participants will be removed from the study if:

- Any clinical adverse event (AE), laboratory abnormality, intercurrent illness or other medical condition occurs such that continued participation in the study would not be in the best interest of the subject
- If the participant requires chronic antimicrobial therapy. For example, children who are found to be infected with HIV will be referred for trimethoprim-sulfamethoxazole prophylaxis and anti-retroviral eligibility evaluation and removed from the study
- Participants who miss ≥ 2 consecutive routine visits will be removed from the study

Participants may withdraw voluntarily from the study at any time.

### Handling of Withdrawals

Participants who withdraw from the study with on-going AEs will be asked to return for follow-up. Specialized tracers have been designated to help to locate participants who do not return for follow-up visits. They will go to the house of the participant (directions are given at enrollment) and try to find the participant or a family member. The staff members will return to try to find any participant who missed a scheduled visit. If the participant is not available, the staff member will ask about the child’s general health, if it is known.

We anticipate some children will not complete the full year of follow-up either due to migration or voluntary withdrawal, so we have chosen to enroll an excess of participants to allow for this loss. Participants who leave the study prematurely will not be replaced.

### Termination of Study

The study may be terminated at the discretion of DMID. As described below, the DSMB may chose to recommend closure of the study after the interim analysis or at another time if new concerns arise.

# Study Intervention/Investigational Product

All medications will be shipped to Fisher BioServices and then distributed to Malawi.

| **Medication (trade name)** | **Manufacturer** | | **Source** | **Formulation** | **Dose** | **Number to receive this medication** |
| --- | --- | --- | --- | --- | --- | --- |
| Chloroquine  (Nivaquine) | Sanofi-Aventis, France | | Shipped by manufacturer | Tablet  100 mg | Days 0,1:  10 mg/kg  Day 2:  5 mg/kg  Medication will be administered to the nearest 1/4 tablet. | 640  (160 monotherapy 480 in combination) |
| Artesunate | Sanofi-Aventis  France or Guilin pharmaceuticals | | Shipped by manufacturer (Arsumax) or  Atlantic laboratories (Guilin product) | Tablet  50 mg | Days 0, 1, 2:  <10 kg ½ tablet  10-15 kg 1 tablet  16-20 kg 1-1/2 tablets  21-30 kg 2 tablets  31-40 kg 3 tablets  >40 kg 4 tablets | 160 |
| Azithromycin | Pfizer, USA or Pliva, USA | | Donated by Pfizer or purchased through Premium Health Services | Suspension  200 mg/5cc | Days 0, 1, 2:  30 mg/kg for 3 days | 160 |
| Atovaquone-proguanil  (Malarone) | GSK, USA | Purchased through Premium Health Services | | Pediatric tablet (PT): 62.5 mg/25 mg  Full strength tablet (FST):250 mg/100 mg | Days 0, 1, 2:  5-8 kg: 2 PT  9-10 kg: 3 PT  11-20 kg: 1 FST  21-30 kg: 2 FST  >30 kg: 3 FST | 160 |

## Modification of Study Intervention/Investigational Product for a Participant

The doses will not be modified.

## Study product acquisition

Atovaquone-Proquanil (Malarone) and Azithromycin (Zithromax) are both U.S. approved drugs.  The azithromycin will either be donated by Pfizer or purchased from Premium Health Services and AP will be purchased from Premium Health Services. These study drugs will be sent to the DMID Clinical Agents Repository (Fisher Bioservices, Rockville, MD) for labeling, storage, and distribution to sites.

Chloroquine sulfate (Nivaquine) and Artesunate are not U.S. approved drugs.  Nivaquine will be acquired from the manufacturer, Sanofi-Aventis France. Artesunate will be purchased from Sanofi-Aventis , or, alternatively, artesunate manufactured by Guilin Pharmaceutical Company will be purchased through Atlantic Laboratories in Thailand.  Sanofi-Aventis and Atlantic laboratories will ship the investigational drugs to the DMID Clinical Agents Repository (Fisher Bioservices, Rockville, MD) for labeling, storage, and distribution to sites.

All study drugs will be labeled for investigational use only.

## Product Storage and Stability

The chloroquine and AP tablets should be stored at 25°C, with excursions from 15-30°C permitted. The artesunate should be maintained below 25°C and should be protected from light and moisture. The azithromycin dry powder and constituted suspension should be kept at less than 30°C. The medications will be kept in an air conditioned, locked storage area that maintains a temperature at or below 25°C. A working supply of the drugs will be kept in the dispensary only during the time of the dispensing and will return to the temperature controlled storage room when dispensing is finished for the day. Reconstituted azithromycin will remain in the refrigerator in the dispensary The storage room and the refrigerator in the dispensary will have temperature monitoring with minimum/maximum thermometers read daily by a member of the staff.

All tablets will be crushed for participants who are unable to swallow pills. Tablets will be crushed according to the study standard operating procedure. We do not have specific data about the potency of crushed artesunate pills, but this method of administration is standard practice in pediatric clinical trials of malaria drug efficacy on which most published artesunate efficacy and safety data are based.

## Accountability Procedures for the Study Intervention/Investigational Product(s)

The DMID Clinical Agents Repository (Fisher Bioservices) will ship study medications to the investigational site in Blantyre, Malawi.

When it arrives at the clinic in Blantyre, the supply manager, or a trained designee, will be responsible for taking inventory of all study treatment. Each day, a nurse pharmacist will be responsible for documenting and dispensing all study medication. The study coordinator or another investigator will be responsible for reviewing inventory and dispensary medication records to be sure that all drugs are accounted for. This inventory reconciliation will take place every 4-6 weeks. Standard operating procedures will be developed to address acquisition, transportation, storage and accountability for study drugs.

## Assessment of Subject Compliance with Study Intervention/Investigational Product

All medication will be administered under direct observation on the day of enrollment and when the subject returns for follow-up on days 1 and 2. The tablets will be crushed and administered with water for participants who are unable to swallow pills.

## Concomitant Medications/Treatments

Children who are receiving chronic therapy with any antimicrobial agent will not be eligible for the study. Short term therapy with antimicrobial agents is permitted in order to treat acute infections that develop during the study period. If participants develop the need for chronic medication, they will be terminated from the study.

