- The prevalence of parasites with the mutation *pfcrt* 76T in cases of recurrent parasitemia after therapy

Because the genetic marker for CQ resistance is well-defined, we have the unique opportunity to assess not just resistance that is manifest on the clinical level, which may be confounded by acquired immunity, but also on the molecular level.

1. To assess the effect of each treatment arm on anemia at the end of study participation.

- Hemoglobin level without parasitemia at the close of the study

Childhood anemia is multifactorial in impoverished regions in sub-Saharan Africa and leads directly and indirectly to increased morbidity and mortality. Malaria is an important contributor to this pervasive problem (54). In our effort to simulate the public health implications of various antimalarial drug policies, we will attempt to assess the effect of each treatment arm on the general well-being of the children by measuring rates of anemia at the close of the study. We will not use the hemoglobin level at the start of the study as a point of comparison because all children will be enrolled with an episode of malaria, which will often be an acute cause of anemia. We will compare the prevalence of anemia, defined as hemoglobin <8 g/dL, at the end of one year of follow-up among all four arms.

1. To assess the safety of repeated use of the drugs in each of the study arms.

- Renal and hepatic function
- Neurological examination

Some of these medications have been associated with mild, transient abnormalities in hepatic and renal laboratory tests. We will assess these side effects in the context of repeated dosing over the course of the year. In addition, we will monitor the neurologic function of the participants due to the unique concerns associated with artemisinin derivatives.

1. To determine the chloroquine blood levels at which chloroquine sensitive and resistant parasites are able to cause infection.

- Chloroquine pharmacokinetic curve for the population
- Drug concentration at the time of parasitemia

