### Rationale for Exclusion Criteria

*Signs of severe malaria.* Children who are too ill to be managed at the outpatient research clinic will be referred to the hospital for management of their severe disease. Once enrolled in the study, children who develop severe malaria will be managed at the pediatric research ward at the referral hospital, but will remain in the study.

*Chronic medication with any antibiotic or antimalarial medication.* Participants who are chronically medicated with a drug that has antimalarial activity (defined as administration of a drug for more than 14 days) will have a decreased risk of acquiring malaria. This medication will interfere with our primary measure of annual incidence of malaria.

*Previous enrollment in this study.* Children who have been enrolled in the study may be infected with parasites that do not reflect the general circulating parasite genetics. Children who have completed the study or have been terminated from the study are not eligible to enroll again.

*Laboratory values more than 3-5x the upper limit of normal.* Abnormal liver and kidney function will interfere with our ability to assess the safety of the study drugs. Because the children will be acutely ill upon recruitment, moderate laboratory abnormalities may be due to acute illness, especially mildly elevated liver enzymes. Overt signs of hepatic or renal failure will be exclusion criteria (described below). Normal values for children based on studies in southern Mozambique will be used (Quinto, et al. Tropical Medicine and International Health submitted, 2006). The exact values to be used are listed in Appendix III.

*Evidence of chronic disease or severe malnutrition.* Children who have underlying illnesses may be difficult to assess for clinical cure from malaria. In addition, children with a chronic progressive disease may be mistakenly determined to have adverse effects of the drugs.

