## Rescue therapy

Rescue therapy will be administered to children who develop clinical treatment failure within the first 14 days after a treatment episode or who are unable to complete an adequate treatment regimen due to AEs. Rescue therapy will be recorded on the CRF. Rescue therapy for uncomplicated malaria will be based on the national treatment guidelines in Malawi. For children who develop signs or symptoms of severe malaria, parenteral therapy will be administered at the Paediatric Research Ward at the hospital. Treatment that is administered by the study team or by the Paediatric Research Ward staff after complete evaluation will not lead to removal of the participant.

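### The exit rules in Protocol 6.6 and 5.4.3 differ, and a child whose study drug is stopped for toxicity has no stated route other than leaving the study

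*Protocol*

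**What the plan says.** **Chronic medication.** Section 6.6 (Concomitant Medications/Treatments) has three sentences. The first bars children on chronic antimicrobials from entry. The second reads "Short term therapy with antimicrobial agents is permitted in order to treat acute infections that develop during the study period". The third is "If participants develop the need for chronic medication, they will be terminated from the study". Section 5.4.3 (Reasons for Withdrawal) states the ground as "If the participant requires chronic antimicrobial therapy", with prophylaxis for HIV-infected children as its example. Section 5.2.1 explains chronic use as "defined as administration of a drug for more than 14 days", in a sentence about drugs with antimalarial activity.

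**Adverse events.** Section 5.4.3 removes a child for an adverse event, laboratory abnormality or illness "such that continued participation in the study would not be in the best interest of the subject". The atovaquone-proguanil row of Appendix II ends enrollment when a transaminase abnormality has not resolved by the next treated episode. No other row has this provision, although the artesunate row also lists a slight transaminase rise.

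**After exit.** Section 11.3 counts primary follow-up time only while the child is enrolled. Section 3.2.2 compares anemia "at the end of one year of follow-up among all four arms" and names renal, hepatic and neurological function as outcomes of repeated use. Section 7.5 offers one early termination visit if the family is willing. Section 5.4.4 asks children who withdraw with ongoing adverse events to come back.

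**The concern.** There are two separate problems.

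First, the wording of 6.6 covers more than that of 5.4.3. A child who starts long-term treatment with a drug that is not an antimicrobial stays under one section and leaves under the other. Staff have no way to tell which applies, and different staff may decide differently.

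Second, the protocol has no state between being on assigned treatment and being out of the study once study drug is judged unsuitable for good. Assessment of repeated use depends on follow-up of the children who tolerated the drug badly. If they leave when toxicity appears, the later safety tests and the one-year hemoglobin come from a group selected for tolerance. In an open-label trial, the removal decision is also made by staff who know the arm. The Appendix II provision is written for one arm and concerns hepatic function, a named safety outcome, so loss could differ between arms on that outcome.

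**Working it through.** **1. Chronic medication: the passages compared.**

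| Place | Trigger as worded | Consequence |
|---|---|---|
| 5.4.3 | chronic antimicrobial therapy | removed |
| 6.6 | chronic medication, unqualified | terminated |
| 5.2.1 | more than 14 days, for drugs with antimalarial activity | definition used for exclusion at entry |

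The triggers in the first two rows differ, so the conflict is on the page. The 14-day definition does not extend 6.6 to other drugs, because it is given only for drugs with antimalarial activity.

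**2. Toxicity: which children stay and which leave.**

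| Situation | Place | Stays in study? |
|---|---|---|
| Course not completed because of adverse events; rescue given by the study team or ward | 6.7 | yes |
| Severe malaria after enrollment | 5.2.1 | yes |
| Third dose vomited, after day 0 of the enrollment illness | Drug administration | yes |
| Adverse event or laboratory abnormality meeting the best-interest test | 5.4.3 | no |
| Transaminase abnormality unresolved at next episode, atovaquone-proguanil row | Appendix II | no |

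The first three rows cover children who miss study drug for one episode. No row covers a child who stops study drug permanently and remains under observation.

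**3. The plan's own figure.** Section 11.2 gives a 95% half-width of about 0.10 for the difference in anemia rates, at a rate of 0.2 with about 120 children per arm. 1.96 × √(2 × 0.2 × 0.8 / 120) = 0.101, so it reproduces. The present point does not make it wrong.

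**4. Possible size for the primary rate (illustration).** The protocol gives no removal rate. Assume that a fraction q of treatment courses, including the enrollment course, leads to immediate removal.

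- From 11.2: control rate m = 1.5 per year. The previous study had mean 2.5 and SD 2, so the between-child squared coefficient of variation is v = (4 − 2.5)/2.5² = 0.24. A gamma distribution of rates between children is assumed.
- Children removed = 1 − (1 − q)S, with S = (1 + qmv)^(−1/v).
- Mean time T for those not removed at enrollment = [1 − (1 + a)^(−k)]/(ka), with a = qmv and k = 1/v − 1 = 3.167.
- Person-time lost = 1 − (1 − q)T.
- Observed rate = [(1 − S)/q]/T.

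| q | S | T | Children removed | Person-time lost | Observed rate |
|---|---|---|---|---|---|
| 0.02 | 0.9705 | 0.9852 | 4.9% | 3.5% | 1.4725/0.9852 = 1.495 |
| 0.05 | 0.9284 | 0.9636 | 11.8% | 8.5% | 1.4327/0.9636 = 1.487 |

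The rate falls by 0.4% and 0.9% from 1.5. The primary comparison would barely move even if removal occurred in one arm only. What is lost is the safety and one-year data of the removed children.

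**The case against.** The strongest reply is that 6.6 should be read in context. The two sentences before the disputed one concern antimicrobials, so the third may simply complete the contrast between short-term and chronic use and restate 5.4.3 loosely. That is a fair reading and may be what was meant. But the sentence is a mandatory exit rule without a qualifier, so it still needs correction.

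On adverse events, the reply is that an event does not remove a child by itself. The best-interest test must be met, and section 6.7 gives rescue to children "or who are unable to complete an adequate treatment regimen due to AEs" and says that such treatment, after complete evaluation, "will not lead to removal of the participant". Observation does not stop completely either, because sections 5.4.4, 7.5 and 9.4 provide for follow-up of events and a termination visit with blood tests and a neurological examination. All of this stands and narrows the point. It does not fill the gap: none of these provisions yields further malaria incidence, the remaining tests at visits 4, 8 and 13, or a one-year hemoglobin.

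A reader might infer more: that anemic children are removed because their treatment lasts over 14 days, so that one-year anemia is understated. The arithmetic is easy. If a share f of anemic children left and no others did, a prevalence of 0.20 would be observed as 0.2(1 − f)/(1 − 0.2f), which is 0.184, 0.158 or 0.111 for f of 10%, 25% or 50%. But no passage removes a child for anemia or mentions its long-term treatment, the 14-day definition does not cover such treatment, and every value of f is invented. The documents do not support this reading.

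**Conclusion.** Two limited points hold. Sections 6.6 and 5.4.3 word the chronic-medication ground differently. And where the best-interest bullet of 5.4.3 or the atovaquone-proguanil row of Appendix II applies, leaving the study is the only stated outcome, so children can be lost selectively for toxicity, an outcome of the repeated-use safety objective.

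The size cannot be derived from the protocol. Under the assumed 2% to 5% removal per course, the effect on the primary rate is below 1%. The cost falls on safety and one-year data, and on the comparison of arms if removal differs between them. It would be too strong to say that the one-year comparison is no longer between randomised arms, or that any adverse event ends participation. This is a low-cost improvement, not a defect that endangers the primary result.

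**What to change.** 1. Reconcile 6.6 with 5.4.3, and the atovaquone-proguanil row of Appendix II with 5.4.3, so that each ground for leaving is stated once and in the same terms. Which clinical rule applies is for the sponsor and investigators to settle.
2. In 5.4.3, define stopping study drug separately from removal from the study. In the first case, continue the four-weekly visits, the tests at visits 4, 8 and 13, and the one-year hemoglobin, unless consent is withdrawn or the visits themselves are against the child's interest.
3. State in 11.3 that smear-positive episodes in these children count in the assigned arm, with their person-time.

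The decision on who stops study drug is unchanged. The cost is protocol wording, since the visits are already scheduled for every enrolled child. The drawback is that some counted episodes will have been treated with non-study drug, which 11.3 already accepts for smear-positive episodes treated at the hospital.

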## Rescue therapy

Rescue therapy will be administered to children who develop clinical treatment failure within the first 14 days after a treatment episode or who are unable to complete an adequate treatment regimen due to AEs. Rescue therapy will be recorded on the CRF. Rescue therapy for uncomplicated malaria will be based on the national treatment guidelines in Malawi. For children who develop signs or symptoms of severe malaria, parenteral therapy will be administered at the Paediatric Research Ward at the hospital. Treatment that is administered by the study team or by the Paediatric Research Ward staff after complete evaluation will not lead to removal of the participant.

# Study Schedule

Refer to Appendix I for the complete study schedule.

## Screening

Prior to any study-related screening procedure, study nurses will approach potentially eligible subjects waiting to be seen by the government clinical officer at the Ndirande Health Centre. The parents/guardians of potential participants will be invited to have the child assessed by a study clinician for possible participation in the study. All of these children will undergo a finger prick for a malaria smear and hemoglobin measurement, as part of the routine care of ill children in this region and at the Ndirande Health Centre. Those who may be eligible will be offered the choice of undergoing screening to potentially enroll in the study or receiving free treatment for their current illness without participating in the study. Subjects who do not meet inclusion criteria or who are for any other reason determined to be too ill for inclusion in the study, or who decline to participate in the study, will receive standard and appropriate treatment, including transport to the Paediatric Research Ward at the Queen Elizabeth Central Hospital for parenteral therapy when indicated for severe malaria.

During the informed consent process, a study clinician will explain the study and review the informed consent form with the participant’s parent/guardian. The family will then have the opportunity to read the form and ask questions. The parent/guardian will be asked to sign the form. If the individual is unable to sign his or her name, a thumbprint will be placed on the form and another individual will be asked to sign the form as a witness. The document also allows the parents/guardians to indicate how to handle the remaining specimens after the study procedures have been completed. Any use of study samples that is outside the scope of the objectives of this protocol will be submitted for prior review and approval by the appropriate IRBs. A single informed consent document will be signed and dated for screening and enrollment. The parent/guardian will be given a copy of the consent form at the time of enrollment. The informed consent process is described in more detail in section 14.

## Enrollment/Baseline

After informed consent is obtained, a case record form including demographic information, previous medication exposure, allergy history and physical examination will be completed. The clinician will ask the parents/guardians about their plans to remain in the area and their willingness to bring the child for all scheduled and unscheduled follow-up. If the participant remains eligible, a study number will be assigned. The participant will be sent to the laboratory for venipuncture to obtain a complete blood count, ALT, creatinine, chloroquine level CBC and parasites for cryopreservation. Two attempts will be made to obtain these specimens. If the technicians are unable to obtain a sufficient specimen, the finger will be pricked to obtain 0.5 mL for a complete blood count, ALT and creatinine. All enrolled children will be escorted home where the location of the household will be recorded using GPS. At home, a questionnaire on socioeconomic status based on household assets will be administered and detailed directions of their home recorded to facilitate active follow-up.

